#### Hospital anxiety and depression scale (HADS) [48]

The HADS is a 14-item self-report scale assessing anxiety (7 items) and depression (7 items). Respondents rate their emotional distress based on the past 7 days using a 4-point scale (from 0 to 3). Possible scores for each sub-scale range from 0 to 21. Scores from 0 to 7 are categorised as normal, from 8 to 10 mild, from 11 to 14 moderate, and from 15 to 21 severe [47]. The HADS is routinely used in CR [28], and has shown good internal consistency for both subscales (i.e. Cronbach’s alpha, anxiety = 0.85, depression = 0.80, total scale = 0.89) [51].

#### Impact of Events Scale – Revised (IES-R) [52]

The IES-R is a 22-item self-report measure that assesses subjective distress caused by traumatic events. For this study, participants will be instructed to answer the items with respect to their recent heart event. Respondents rate the items based on the past 7 days using a 5-point scale ranging from 0 (not at all) to 4 (extremely). This scale yields a total score ranging from 0 to 88 and three subscale scores: Intrusions, Avoidance and Hyperarousal. Scores of 24 to 32 indicate post-traumatic stress disorder is a clinical concern, whereas scores of 33 to 88 indicate a diagnosis of post-traumatic stress disorder [52]. The IES-R subscales have good internal consistency (Cronbach’s alphas range from 0.79 to 0.91) [52].

#### Metacognitions Questionnaire 30 (MCQ-30) [53]

The MCQ-30 is a 30-item self-report scale that measures five different domains of metacognition (cognitive confidence, positive beliefs about worry, cognitive self-consciousness, negative beliefs about uncontrollability and danger, need to control thoughts). Respondents rate how much they “generally agree or disagree” with the statements presented on a 4-point scale (1, do not agree; 2, agree slightly; 3, agree moderately; 4, agree very much). This questionnaire yields a total score ranging from 30 to 120 and four subscale scores. High scores indicate, respectively, lack of cognitive confidence, more positive or negative beliefs about worry, increased tendency towards cognitive self-consciousness, and greater belief in the need to control thoughts. The MCQ-30 subscales have good internal consistency (Cronbach’s alphas range from 0.72 to 0.93) [53–55].

#### European Quality of Life 5 Dimensions 5 Levels (EQ-5D-5 L) [56, 57]

The ED-5D-5 L is a standardised questionnaire for use as a measure of health status and its use is recommended in the National Institute for Health and Clinical Excellence guidelines for economic evaluation [58]. The tool assesses five health dimensions: mobility, self-care, usual activities, pain/discomfort and anxiety/depression. Each dimension has five response options: no problems, slight problems, moderate problems, severe problems and extreme problems. In addition, respondents also rate their overall health on a 0–100 vertical visual analogue scale. The measure has been shown to be valid and reliable in a cardiovascular population [59].

#### Economic Patient Questionnaire (EPQ)

The EPQ is designed to collect data on outpatient services and non-hospital-based health and social care use. The EPQ assesses three areas, namely use of primary and community-based health services, social support services accessed outside the hospital, and aids and equipment used as part of care.

#### Cognitive Attentional Syndrome Scale-1 revised (CAS-1R)

The CAS-1R has been adapted for the present study from the original Cognitive Attentional Syndrome Scale-1 [30], a 16-item self-report questionnaire assessing an individual’s metacognitive beliefs, knowledge and strategies. The CAS-1R includes 10-items assessing the degree to which individuals have been worrying and/or focusing attention on threats, the degree to which individuals hold negative metacognitive beliefs about worry and the degree to which individuals hold positive metacognitive beliefs about worry. Each CAS-1R item is scored on a scale from 0 to 100 with higher scores indicating more use of unhelpful metacognitive strategies or greater conviction in metacognitive beliefs.

#### Sociodemographic and clinical data questionnaire

This questionnaire is designed to collect sociodemographic information and clinical data. Sociodemographic information will be collected only at baseline and includes age, sex, ethnicity, marital status, living arrangements, employment status and educational attainment. Clinical data to be collected at each time-point includes height, weight, smoking status, alcohol use, cardiovascular events, other health conditions, and details about medications for anxiety, depression and psychological therapies.

In addition to the measures included above, CR staff will complete a CR register for each participant detailing the number of exercise sessions and educational talks attended. The CR register will provide details to assess adherence to usual CR. Adherence to CR has been defined as the attendance to four or more sessions to each component of usual CR (exercise sessions and educational talks).

### Qualitative evaluation

Participants allocated to the intervention group will be interviewed, including those who complete the intervention, those who only complete part of it, and those who do not engage with any part of the intervention. Participants will be sampled purposively to include ranges of age and psychological distress, and levels of participation. Sampling will stop when theoretical saturation is reached. In semi-structured interviews, participants will be prompted to talk about (1) their emotional experience since the index event, (2) their reactions and expectations on being offered the intervention and (3) their experience of undertaking it.

Interviews will be semi-structured and conversational in style, and an interview guide will be used. Interviews will be conducted by telephone or face-to-face, as preferred by each participant, audio-recorded, transcribed verbatim and anonymised for analysis.

### Sample size calculation

The sample size is based on having sufficient numbers of participants to evaluate acceptability and feasibility, and to obtain provisional evidence for effectiveness. To these ends, the aim is to recruit 108 participants in total. Anticipating a 25% attrition rate, this will provide a final *n* = 40 in each arm, i.e. a total of 80 participants. With this sample, overall recruitment and retention rates for a full-scale trial will be estimated with an error of plus/minus 8% at most. This sample is also more than adequate for estimation of variability in outcome measures for which samples of 40 are generally sufficient [60].

Based on our experience of previous phases of the PATHWAY programme, 10.5 patients have been recruited for every 100 referrals, over 12 months, across three different sites. Following this figure and based on the number of annual referrals provided by the two participating sites on this phase of the PATHWAY programme, we estimate recruiting 8–9 patients per month, across both sites, over 12 months.

Feasibility trials are not powered to provide a definitive effectiveness analysis [59]. Therefore, evaluation of effectiveness will focus on effect size estimates and confidence intervals rather than statistical significance.

### Analyses

The trial will be analysed using quantitative, qualitative and economic methods.

### Economic analysis

The economic analysis will explore the potential of Home-MCT to be cost-effective to provide a preliminary estimate of cost-effectiveness and inform the design of future evaluations. A cost-effectiveness acceptability analysis will be conducted from the perspectives of health and social care providers and patients, the key stakeholders in treatment decisions. The time horizon for the primary economic analysis will be at 12-month follow-up.

The primary measure of health benefit is Quality Adjusted Life Years, which will be estimated from the EQ-5D-5 L [56, 57] and the utility tariffs recommended by NICE at the time of the analysis [58]. At the end of the trial, a data request will be submitted to NHS Digital to obtain data on hospital-based service use covering all assessment points (baseline, 4- and 12-month follow-up). To supplement these data, the EPQ will be used at baseline, 4- and 12-month follow-up. Each item of resource use will be multiplied by the unit cost specific to that item. Standard national unit costs will be used. Single imputation will be used to impute missing baseline values for costs, utility and key covariates. Multiple imputation will be used to impute missing observations from participants who complete follow-up, and missing follow-up data for participants lost to follow-up.

The primary and sensitivity economic analyses will control for key baseline covariates or characteristics identified in the study. Cost-effectiveness acceptability curves will assess the likely cost effectiveness of the intervention and uncertainty in the observed data. This approach re-values outcomes in monetary terms. However, in the UK, there is no universally agreed monetary value for the types of outcome measures used in cost effectiveness analyses. An approach used in healthcare is to ask the question: what is the maximum amount decision-makers are willing to pay to gain one unit of outcome? An analysis of decisions made by NICE suggests a range of implicit values between £15,000 and £30,000 for the amount a decision-maker is prepared to pay to gain one Quality Adjusted Life Year. This hypothetical threshold willingness-to-pay values will be used to estimate the probability that an intervention is cost-effective.

Sensitivity analysis will assess uncertainty due to design decisions. Within trial analyses include using a 4-month time horizon, varying the assumptions and components used to estimate the unit cost of Home-MCT and using alternative measures of health benefit (primary and key secondary clinical outcomes). In addition, decision modelling will be used to extrapolate over longer time horizons of 2 and 5 years.

### Trial management and oversight arrangements

This trial is part of a larger research programme funded by the National Institute of Health Research under its Programme Grants for Applied Research scheme (RP-PG-1211 20,011). The programme is overseen by an independent programme steering committee which meets every 6 months to provide expert advice, supervise the overall programme on behalf of the National Institute for Health Research and the sponsor, and monitor progress against agreed milestones. A programme executive committee comprising the chief investigator, co-investigators, the core project team and other relevant parties meets quarterly. Notwithstanding the legal obligations of the sponsor and chief investigator, the executive committee has operational responsibility for the conduct of the trial, including monitoring overall progress to ensure adherence to the protocol and for taking appropriate action to safeguard participants and the quality of the trial. A programme management group comprising the chief investigator and core project team meet weekly to oversee the day-to-day management of the programme. There is also a service user advisory group which meets at least every 6 months and provides advice and feedback on a range of trial-related activities, e.g. reviewing study documents.

### Data management

Participants will be randomly allocated a study identity code number for use on all study documents. The research team will create a confidential database of each participant’s name, date of birth and study identity code to permit identification of participants enrolled in the study, e.g. for follow-up. All study documents will be held in strictest confidence and access to study documents will be restricted to authorised persons. Participant consent forms will be filed in the corresponding site file and in participants’ medical notes. Baseline and follow-up data, which is anonymous data, will be stored in locked filing cabinets at GMMH. These data will be entered into an electronic database for analysis purposes by study team members blind to trial arm allocation. All computers are password protected and adhere to the secure storage policies of the NHS trust and University of Manchester.

Ten percent of the data entered electronically from each of the three time points (baseline, 4- and 12-months follow-up) will be selected at random and quality checks will be performed by the statistical team. Any discrepancies will be noted, corrected and counted to obtain an error rate. Depending on the error rate, further checks will be performed.

### Safety reporting

Plans and procedures are in place for negative changes in participants’ psychological state. Health professionals delivering the Home-MCT scripted telephone calls will monitor any potential adverse events (AEs) or serious adverse events (SAEs) over the time of the intervention. Two hypothesised AEs that might occur due to the Home-MCT intervention are lowered mood and suicidality as a result of discussing current health status, reducing or terminating usual treatment in the event that a patient finds Home-MCT particularly helpful. Although it is acknowledged that thinking or talking about distress can worsen mood, this is rare and usually transient. Any AEs will be recorded at the study site using an AE form, which will be completed by the health professionals. These will be reported to the research team and reviewed for seriousness and causality by a designated sub-investigator who is not blind to treatment allocation. Any that are deemed SAEs, and are related to the intervention, will be reported to the ethics committee, the programme steering committee and the sponsor’s Research and Innovation Manager within 7 days of the event. AEs and SAEs will be reviewed on a quarterly basis at the programme’s executive committee meetings.

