#### Home-MCT alongside usual CR (intervention group)

The intervention group will receive Home-MCT in addition to the usual CR.

Home-MCT consists of a self-help manual comprising six modules. Members of the PATHWAY programme’s service user advisory group provided feedback on the structure and user-friendliness of the Home-MCT manual. Suggested changes were implemented before commencing recruitment to the trial.

Participants will complete the Home-MCT manual at their own pace over 6–8 weeks. It is anticipated that participants will complete one module per week, but flexibility in rate of progress will be permitted. The Home-MCT modules focus on modifying the specific metacognitive beliefs and processes that maintain anxiety and depression. Modules comprise well-specified techniques for developing new strategies to overcome worry and rumination, and modifying the metacognitive beliefs that maintain unhelpful patterns of thinking. Participants will be instructed to practise the techniques introduced in each module and to complete tasks between modules.

Participants will receive three scripted telephone calls (up to 30 minutes each) from trained CR staff (e.g. nurses, occupational therapists) over the course of the intervention. The first telephone call will provide an overview of the Home-MCT manual and the remaining two will offer support and guidance on completing the modules and implementing Home-MCT strategies. The first telephone call will be delivered before the participant starts the manual and the remaining ones after the completion of modules 2 and 4. The CR staff will be asked to follow a structured script when making telephone contact. Their role is to provide support and guidance on completing Home-MCT.

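### As the article states it, adverse-event monitoring rests with the Home-MCT callers during the 6–8 week intervention, so AE-form counts come from one arm only, and calls 2 and 3 have no date for participants who stall

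*Protocol article*

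**What the plan says.** Safety reporting in the protocol article fixes three things.

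- Who monitors, and when: "Health professionals delivering the Home-MCT scripted telephone calls will monitor any potential adverse events" and serious adverse events, over the time of the intervention.
- Who records: AEs are "recorded at the study site using an AE form, which will be completed by the health professionals".
- What happens next: a sub-investigator who knows the allocation reviews each event for seriousness and causality. Serious events judged related go to the ethics committee, the steering committee and the sponsor within 7 days. All AEs and SAEs are reviewed quarterly by the executive committee.

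The same section names the harms it has in mind: "Two hypothesised AEs that might occur due to the Home-MCT intervention are lowered mood and suicidality", together with reducing or ending usual treatment. It adds, of mood worsened by thinking or talking about distress, that "this is rare and usually transient".

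The calls are described only in the section on the intervention group: "Participants will receive three scripted telephone calls (up to 30 minutes each) from trained CR staff". The first comes "before the participant starts the manual and the remaining ones after the completion of modules 2 and 4". The section on usual cardiac rehabilitation (CR) describes no such calls for controls.

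**The concern.** AE monitoring has been attached to a component of the treatment under test. Three things follow if sites do what the article says.

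1. AE forms come from one arm, for a short part of follow-up. A table of AEs by arm built from them would reflect who was asked.
2. The sub-investigator judges relatedness without knowing how often low mood or suicidal thoughts occur under usual CR alone. That judgement also decides which serious events are reported within 7 days.
3. Within the intervention arm, the only timing given for calls 2 and 3 is progress through the manual. A person whose mood falls because of the material may be the one who stops working through it, and then neither trigger is reached. The article expects such people: the qualitative evaluation plans to interview part-completers and those who never engage.

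One aim of the trial is to inform the design of a full-scale trial, where the same rule could be carried forward.

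**Working it through.** **Inputs, all from the protocol article.** Intervention length 6–8 weeks, six modules, and three calls with the timing quoted above (Home-MCT section). Participant involvement 12 months, taken as 52 weeks (Participant timeline). 108 participants allocated 1:1, so 108/2 = 54 per arm (Sample size; Recruitment and allocation). The article gives no figure for AE coverage, so there is none to reproduce.

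**Time covered by the described route.** Credit the whole intervention period as monitored, which is the generous reading.

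- Intervention arm: 6/52 = 11.5% to 8/52 = 15.4%. Weeks with no described AE monitor: 52 − 8 = 44 to 52 − 6 = 46.
- Control arm: 0 of 52 weeks.
- Both arms together: (54 × 6)/(108 × 52) = 5.8% to (54 × 8)/(108 × 52) = 7.7% of planned person-time.

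**What one-armed collection does to counts.** Suppose 5%, 10% or 20% of participants in each arm had an AE during the window. These risks are assumed, since the article gives none. Expected numbers per arm are 54 × 0.05 = 2.7, 54 × 0.10 = 5.4 and 54 × 0.20 = 10.8. The described route could pick these up in the intervention arm and would pick up none in controls, although the true risks are equal.

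**Dated calls after the manual is started.** At an even pace module *k* ends at *k* × (6 to 8)/6 weeks after starting.

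- Module 2: 2 × 6/6 = 2.0 to 2 × 8/6 = 2.7 weeks.
- Module 4: 4 × 6/6 = 4.0 to 4 × 8/6 = 5.3 weeks.
- Time left after module 4: 6 − 4.0 = 2.0 to 8 − 5.3 = 2.7 weeks, with no later call.

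Calls triggered after starting: none for someone who stops before finishing module 2, one for someone who stops between finishing modules 2 and 4, two for someone who finishes module 4.

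**Data that both arms do supply.**

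| Source | Content | Linked to the AE form, causality review or SAE reporting? |
|---|---|---|
| HADS at 4 and 12 months | "Respondents rate their emotional distress based on the past 7 days using a 4-point scale" | No |
| Clinical data questionnaire at each time-point | cardiovascular events, other health conditions, "details about medications for anxiety, depression and psychological therapies" | No |
| NHS Digital request at end of trial | hospital-based service use, for the economic analysis | No |

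These support a limited symmetric comparison of some harms. None is described as asking about suicidality. HADS looks back 7 days, so it can miss a drop in mood that has passed.

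**The case against.** The strongest reply is that this is a condensed article. Safety reporting opens by saying that plans and procedures exist for negative changes in psychological state, and that sentence is not limited to one arm or period. Nor is the statement that AEs are recorded at the study site. The full protocol may describe a control-arm route. This stands as a limit: a reader might infer that control-arm or later AEs go unrecorded, and the article does not say so. It does not remove the point, because the article names a specific monitor, period and recorder, and the general opening sentence names no second route.

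Second, the principal outcomes are acceptability and feasibility, and no between-arm AE comparison is planned. A reader might infer that a planned analysis is invalid; none is stated, so that reading fails. The missing background rate for the causality review remains.

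Third, controls and early stoppers are not out of sight. Both arms are offered weekly CR sessions for 6–8 weeks, sites offer extra support for distress, and patients with particularly high scores are referred to their GP. Together with the data tabulated above, this means it would be wrong to describe 44–52 weeks as unobserved. What is lacking is a described route from any of these contacts to an AE record.

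Fourth, the article says without condition that participants will receive three calls, and that staff monitor throughout the intervention. A reader might infer that early stoppers will not be called. The text does not support that; it supports only that the calls have no date once module progress stalls.

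Finally, one could count HADS look-back days (2 × 7/365 = 3.8%) as a measure of missed harm. HADS is not presented as an AE detector, so that figure does not size the problem.

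**Conclusion.** The point holds within these limits. On the rule the article states, AE-form counts are collected in one arm and for 11.5–15.4% of follow-up. They cannot be compared between arms and supply no usual-CR background rate to the unblinded causality review. In the intervention arm, a participant who stalls before finishing module 2 has no dated AE-monitored call after starting the manual.

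The percentages describe calendar coverage, not missed events, whose number the document does not allow one to estimate. They rest on a 52-week year and on counting the full 6–8 weeks as monitored. The module times assume even pacing, whereas the article allows flexibility.

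Severity is minor to moderate. The harms in question, lowered mood and suicidality, are ones the protocol itself names, and the remedy is cheap. Against that, between-arm AE comparison is not a stated objective, both arms supply related data, and the full protocol may already contain a further route.

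**What to change.** **1. Ask both arms the same question.** Add one item to the clinical data questionnaire that all participants complete at 4 and 12 months: marked worsening of mood, thoughts of self-harm, or stopping usual treatment since the last assessment. Report it by arm. List call-detected AEs separately, labelled as Home-MCT only. Set a prompt risk-response procedure for answers returned by post or online.

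**2. Give calls 2 and 3 a calendar backstop.** Make them after modules 2 and 4, or at weeks 3 and 6 after the planned manual start date agreed at call 1, whichever is sooner. The anchor matters. At the 8-week pace the margins are 3 − 2.67 = 0.33 weeks (2.3 days) and 6 − 5.33 = 0.67 weeks (4.7 days). If the clock ran from call 1 itself, a longer gap before starting would pull on-pace calls forward. Anchored to the planned start date, they stay put for participants who start on that date and keep to 6–8 weeks. Slower participants would be called earlier than now.

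**Cost.** One item on an existing form, the risk-response procedure, and up to two calls of up to 30 minutes for each person who has stopped, within the three already promised. Recall over 4 and then 8 months is imperfect and may differ by arm, because participants know their allocation.

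**Timing.** Recruitment was predicted to end in April 2018, before publication in August 2018, so the call change mainly serves the full-scale trial. The new item could still be used at 12-month assessments, which would run to about April 2019 on that prediction.
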